Matching placebo will be compounded, using a matching empty capsule filled with sufficient quantity of microcrystalline cellulose. The capsules are visually inspected and packed into Polypropylene bottles.

Unblinding may be done in the case of some serious adverse events (SAEs), defined as those which result in death, are life-threatening, require inpatient hospitalization or prolongation of existing hospitalization, result in significant disability or incapacity, or result in congenital anomaly or birth defect, [name] will be notified and if the event is determined to be possibly related to dronabinol it will be discontinued.  Dronabinol will not be discontinued for SAEs determined to be unrelated to dronabinol, such as pain crisis. In the event that a participant withdraws from the study or discontinues dronabinol due to a SAE, the participant will be unblinded.

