# 7 Study Intervention Discontinuation and Participant Discontinuation/Withdrawal

## 7.1 Discontinuation of Study Intervention

For serious adverse events (SAEs), defined as those which result in death, are life-threatening, require inpatient hospitalization or prolongation of existing hospitalization, result in significant disability or incapacity, or result in congenital anomaly or birth defect, [name] will be notified and if the event is determined to be possibly related to dronabinol it will be discontinued.  Dronabinol will not be discontinued for SAEs determined to be unrelated to dronabinol, such as pain crisis. In the event that a participant withdraws from the study or discontinues dronabinol due to a SAE, the participant’s ongoing status will be monitored by [name] until: 1) a resolution is reached, i.e., the problem requiring hospitalization has resolved or stabilized with no further changes anticipated; 2) the SAE is determined to be clearly unrelated to study intervention; or 3) the SAE results in death. In cases where a participant discontinues dronabinol for any reason, the Study

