 Coordinator will ask the participant to continue to attend all study visits and complete assessments. Criteria for discontinuation of the randomization condition include 1) pregnancy; 2) current suicidal ideation with plan or intent; 3) suicide attempt; 4) severe anxiety episode, severe depression episode, or psychotic symptoms; 5) severe adverse events probably or definitely related to the randomization condition, as defined above; 6) adverse events that have the potential to cause serious impairment of health, including ischemic or arrhythmic adverse cardiovascular disease events (e.g., myocardial infarction, unstable angina, coronary revascularization, coronary artery disease, unstable arrhythmias, transient ischemic attack, stroke, or congestive heart failure); 7) serious adverse events, defined as those which result in death, are life threatening, require inpatient hospitalization or prolongation of existing hospitalization, result in significant disability or incapacity, or result in congenital anomaly or birth defect; or 8) the request of participants or their treating providers. [name] or the Study Coordinator will be responsible for informing the participant to discontinue the randomization condition and will ask the participant to continue to attend all study visits. Once the randomization condition has been discontinued it will be for the duration of the study.

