### 8.3.2 Definition of Serious Adverse Events (SAE)

An adverse event (AE) or suspected adverse reaction is considered "serious" if, in the view of the investigator, it results in any of the following outcomes:

- Results in death
- Is life-threatening (i.e., in the opinion of the investigator, the subject is at immediate risk of death from the AE)
- Requires inpatient hospitalization or prolongation of existing hospitalization (hospitalization is defined as an inpatient admission, regardless of length of stay)
- Results in persistent or significant disability/incapacity (a substantial disruption of the subject’s ability to conduct normal life functions)
- Is a congenital anomaly/birth defect
- Constitutes an important medical Important medical events are defined as those occurrences that may not be immediately life threatening or result in death, hospitalization, or disability, but may jeopardize the subject or require medical or surgical intervention to prevent one of the other outcomes listed above. Medical and scientific judgment should be exercised in deciding whether such an AE should be considered serious.

For this study, events not considered to be SAEs are hospitalizations for:

- Routine treatment or monitoring not associated with any deterioration in condition.
- The administration of blood or platelet transfusion as routine treatment of studied
- Emergency outpatient treatment or observation that does not result in admission, unless fulfilling other seriousness criteria
- Hospitalization for treatment of uncomplicated sickle cell pain crisis as defined by the investigator

If an AE is considered serious, both the AE eCRF and the SAE Report Form must be completed. For each SAE, the investigator will provide information on severity, start and stop dates, relationship to study agent, action taken regarding study agent, and outcome.

The principal investigator is responsible for reporting SAEs to the IRB and other applicable regulatory authority. The principal investigator is responsible for submitting follow-up reports for all SAEs regarding the patient’s subsequent course until the SAE has resolved or until the patient’s condition stabilizes (in the case of persistent impairment), or the death of the patient.

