### 8.3.5 Adverse Event Reporting

The reporting of AEs and SAEs will start when the patient signs the informed consent for the study throughout the treatment period and up to and including the 28-day follow-up period. All new AEs occurring during that period must be recorded (if SAEs, they must be reported to the Data Safety Monitoring Committee (DSMC) and IRB as per institutional guidelines). AEs will be recorded per SOPs.

The investigator will report the action taken with study agent as a result of an AE or SAE, as applicable (e.g., discontinuation, interruption, or dose reduction of study agent, as appropriate) and report if concomitant and/or additional treatments were given for the event.

- Patients receiving treatment with dronabinol capsules should be alerted to the potential for additive central nervous system depression if dronabinol capsules is used concomitantly with alcohol or other CNS depressants such as benzodiazepines and barbiturates.

Study agent will be discontinued for all AEs grade 3 or above. Study agent will not restarted until AE has resolved to grade 1 for all objective events or until patient grade 1 or grade 2 and patient requests to restart drug despite symptoms for all subjective events. This is because some adverse events of dronabinol may be seen as a benefit by patients, for example dronabinol may cause tiredness but some patients with SCD complain of insomnia.

Study agent will not be discontinued for expected AEs or SAEs determined to not be due to dronabinol such as a pain crisis.

For patient reported AEs grade 1 or 2 the patient and investigator will decide together whether to discontinue study agent, lower the dose of study agent, or to continue on full dose if the patient feels that the benefit of study agent outweighs the discomfort of the AE of the AE is in fact perceived as a benefit (i.e. sleepiness may be a benefit if the subject previously suffered from poor sleep).

The investigator will report the outcome of the event for both AEs and SAEs. All SAEs that have not resolved upon discontinuation of the subject’s participation in the study must be followed until recovered (returned to baseline), recovered with sequelae, or death (due to the SAE)

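### The rules for stopping, restarting and unblinding study drug contradict each other across sections 6.3, 7.1 and 8.3.5 of the protocol

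*Protocol*

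**What the plan says.** **Section 7.1, opening paragraph.** Stopping after an SAE depends on relatedness: "if the event is determined to be possibly related to dronabinol it will be discontinued". The converse is also stated: "Dronabinol will not be discontinued for SAEs determined to be unrelated to dronabinol, such as pain crisis".

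**Section 7.1, list of criteria.** Criterion 7 is "serious adverse events, defined as those which result in death, are life threatening, require inpatient hospitalization or prolongation of existing hospitalization", and the definition then runs on to disability and birth defect. It carries no relatedness condition. Criterion 5, in the same list, covers severe events and requires a probable or definite relationship to the randomised condition. The list is followed by "Once the randomization condition has been discontinued it will be for the duration of the study". Participants who stop are asked to keep attending visits; the opening paragraph adds completing assessments.

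**Section 8.3.5.** The severity rule is "Study agent will be discontinued for all AEs grade 3 or above". A restart rule follows: "Study agent will not restarted until AE has resolved to grade 1" for objective events, with a looser condition for subjective ones. A later sentence exempts expected AEs or SAEs found not to be due to dronabinol, with pain crisis as the example.

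**Section 6.3.** The unblinding paragraph opens permissively, as something that may happen for some SAEs. It ends: "In the event that a participant withdraws from the study or discontinues dronabinol due to a SAE, the participant will be unblinded".

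**Section 8.3.2.** Among hospitalisations that do not count as SAEs is "Hospitalization for treatment of uncomplicated sickle cell pain crisis as defined by the investigator". The SAE definitions written out in 6.3 and 7.1 do not repeat this exclusion.

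**The concern.** These rules decide whether a participant stays on a psychoactive drug after a serious or severe event, whether the drug may be resumed, and whether the blind is broken. If two sections give opposite instructions for the same event, whatever site staff do departs from one of them, and two similar participants can be handled differently.

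The situation is foreseeable. The protocol uses pain crisis as its own example and schedules collection of emergency visits and admissions at baseline and weeks 4 and 8.

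There is also a statistical side. The primary outcome is the self-reported PROMIS pain impact score, measured as change from baseline to week 8. Section 4.2 explains that the crossover design was dropped because masking failed in the second period. If the stopping rule that is applied also settles whether the allocation is revealed, an ambiguity in safety management becomes an ambiguity in the conduct of the blind.

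**Working it through.** The protocol states no figure on this point, so the check is a comparison of texts. Taking each type of event through each rule gives:

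| Event | 7.1, opening paragraph | 7.1, criteria list | 8.3.5 |
| --- | --- | --- | --- |
| SAE judged unrelated | Continue | Stop (criterion 7) | Continue (exception) |
| SAE judged possibly related | Stop | Stop (criterion 7) | Stop if grade 3 or above |
| Non-serious grade 3 event, unexpected, only possibly related | Not addressed | Criterion 5 not met | Stop |
| Restart after stopping | Not addressed | Never | Allowed once the event has improved to a stated grade |

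**1. Unrelated SAEs.** The first row has opposite instructions inside one section. The two SAE definitions in 7.1 are essentially the same, so they do not refer to different classes of event. Relatedness cannot simply be read into criterion 7, because criterion 5 states it and criterion 7 does not.

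**2. Restart.** Section 7.1 rules out resumption for anyone whose randomised treatment has been discontinued. Section 8.3.5 uses the same verb and then says when resumption is possible. A participant who stops for a grade 3 event that also meets a 7.1 criterion is covered by both.

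**3. Severe events.** Section 8.3.3.1 labels grade 3 as severe, so criterion 5 and the grade rule in 8.3.5 overlap. For an unexpected, non-serious grade 3 event judged only possibly related, criterion 5 does not call for stopping, 8.3.5 does, and the 8.3.5 exception does not apply.

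**4. Unblinding.** Under 6.3, discontinuation because of an SAE leads to unblinding. For an unrelated SAE, following criterion 7 therefore stops the drug and triggers that sentence, while following the opening paragraph of 7.1 does neither. The start of the same 6.3 paragraph treats unblinding as optional, and nothing says whether the arm is disclosed to the treating clinician, the study team or the participant.

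**5. SAE definition.** An admission for uncomplicated pain crisis is outside the SAE definition in 8.3.2, but inside the definitions in 6.3 and 7.1, which include any inpatient hospitalisation.

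**What this reaches in the analysis.** The primary analysis is by intention to treat (9.3, 9.4.1) and follow-up continues after stopping, so the primary set is the same under every reading. The secondary analysis drops participants with less than 4 weeks on study or a pill count below 50% of the optimised dose. If that 50% is taken over the full 8 weeks (the protocol does not say), a fully compliant participant who stops permanently before 0.50 × 8 = 4 weeks is removed, while one who continues or restarts may be kept.

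**The case against.** Several counter-arguments have force.

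- **Section 8.3.5 can be read as a rule with an exception.** This stands. The grade 3 sentence and the later exemption are not counted here as contradicting each other. What remains is the mismatch with criterion 5.
- **Pain crisis can be an SAE in 7.1 without contradicting 8.3.2.** This also stands. Section 8.3.2 excludes only uncomplicated crisis admissions, as judged by the investigator, so a complicated crisis may still be an SAE. A reader might infer a flat contradiction; the text supports only a need to align the definitions.
- **Discontinuation in 8.3.5 may mean a temporary hold.** This is possible as an intention but not as written: the same section lists interruption as a separate action.
- **A designated person is notified of SAEs, so decisions are not left to whoever reads which section.** This limits inconsistency between staff, but that person faces the same conflicting text.
- **For SAEs judged possibly related, both parts of 7.1 stop the drug.** This is correct. The first conflict concerns unrelated SAEs only.

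Two stronger readings are tempting. One is that participants will learn their arm and then report the primary outcome unblinded. Section 6.3 does not say to whom the arm is revealed, and its opening is permissive, so this is a possibility rather than something the protocol prescribes. The other is a numerical loss of treatment effect or power. That would need a rate of admissions or severe events over 8 weeks and an assumption about the benefit lost on stopping; the protocol gives neither.

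**Conclusion.** The point holds as an internal inconsistency in the current text. Three conflicts remain after every reasonable reading: continuing versus stopping after unrelated SAEs, permanent versus reversible discontinuation, and the relatedness threshold for severe events. Section 6.3 adds optional versus automatic unblinding with the recipient unstated, and the SAE definitions in 6.3 and 7.1 need aligning with 8.3.2.

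Staff cannot comply with all sections. Drug exposure, possible unblinding before week 8, and secondary-set membership depend on which section is followed. The intention-to-treat set does not change, and the sample-size figures in section 9.2 are not touched. The size of the effect on the results cannot be quantified from the protocol. The reason to act is that safety instructions conflict, and inconsistent exposure or a broken blind cannot be undone at the analysis stage.

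**What to change.** The sponsor, with the clinical team, should reconcile sections 6.3, 7.1, 8.3.2 and 8.3.5 into one consistent set of rules, preferably a single table to which the other sections refer. It should settle, for each combination of seriousness, grade and relatedness:

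- whether study drug is stopped;
- whether it may be restarted;
- whether a pain-crisis admission counts as an SAE, with one SAE definition used throughout;
- when the arm is disclosed, and to whom.

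This review does not say which of the existing rules is right and proposes none. The cost is one protocol amendment, with the usual ethics review.

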## 7.2 Participant Discontinuation/Withdrawal from the Study

Subjects may discontinue participation at any time by informing an investigator, but there is no plan to discard previously acquired data. Subjects experiencing study agent related adverse events will be encouraged to continue study follow-up until resolution, if feasible.

A subject’s participation may be discontinued at any time by any of the investigators if discontinuation is thought to be in the subject’s best interest, if continued participation is unlikely to yield further useful data due to noncompliance with study procedures, or if the study is discontinued.

## 7.3 Lost to Follow-Up

**Retention strategy.** We will employ several strategies to maximize retention:

1.  Subject tracking. At all visits, we will record: 1) subjects’ address, phone numbers; 2) contact information of family or friends; and 3) locations where subjects work.

2.  Engaging subjects. Frequent contact with study staff helps to keep subjects engaged. As we have done previously, we will contact subjects by phone if they miss a questionnaire. In addition, we will hire study staff who are racial and ethnic minorities consistent with our source population to enhance mutual understanding and engagement.

3.  Subject compensation. To increase feasibility of attending each visit subjects will be compensated $25 per office visit and a two way metro card for cost of travel. Subject compensation will occur through study debit cards.

**Estimates and monitoring for attrition.** In this study, we conservatively estimate attrition of 20%. Retention reports will be included in reports to the DSMC every 6 months.

**Benchmarks and contingency plans.** We will conduct assessments every 6 months to verify benchmarks of: 90% retention rate. If benchmarks are not met, will institute contingency plans such as: adding or reserving more physician time for evaluations, better coordination between research and clinical staff, revising the incentive structure, or making other modification based on reasons for attrition.

# 8 Study Assessments and Procedures

## 8.1 Efficacy Assessments

Informed consent will be obtained prior to screening activities. Screening may take multiple visits but must be completed within 30 days of obtaining informed consent. The following assessments will be completed:

- Written Informed consent
- Demographics
- Medical history - Including SCD type, SCD related problems, other medical problems, psychiatric and substance use history, description of pain and pain treatment
- Weight
- Vital Signs
- Review of current and past medications
- Pregnancy test - For women of child bearing potential Urine or serum.
- Urine test for cannabinoids
- Physical exam
- Baseline Patient Reported Outcomes (ASCQ-Me survey domains for pain impact, emotional impact, social impact, stiffness, and sleep, PROMIS domains for pain impact, neuropathic pain, nociceptive pain, cognitive function, gastrointestinal distress and anxiety. LANSS, PQ-B, C-SSRS)

Data will be collected from five sources: 1) Validated patient reported outcome surveys at baseline, and weeks 4 and weeks 8; 2) Timeline Follow-Back for hospital utilization use at research visits at weeks 4 and 8; 3) medical interview and physical examination at screening, weeks 4 and weeks 8; 4) laboratory markers of inflammation including IL1b, IL4, IL6, IL10, VCAM-1 and TNFα, tryptase, and substance P at baseline, weeks 4 and weeks 8 5) urine toxicology tests at baseline and weeks 4 and weeks 8, 6) safety laboratory tests of renal function, liver function, complete blood count and reticulocytes and pregnancy at screening and at weeks 4 and weeks 8;

In-person screening research interview, screening medical interview and physical examination data will be recorded on paper data collection instruments that identify participants only by unique study ID number. Patient reported outcome surveys will be performed on an I-Pad and entered automatically into REDCap. Data will be entered into a password-protected, encrypted web-based REDCap database, and paper documents will be filed in a locked cabinet.

Urine toxicology tests will be performed at baseline and blood tests for cannabinoids at weeks 4 and weeks 8. Specimens will be labeled with the name of the research study, the date and time of collection, and the specimen number; no names or other identifying information will be used. The specimen number will be generated using the subject’s study ID number, the letters UT (to denote urine toxicology test), and the visit number. The laboratory will run toxicology tests for THC, methadone, opiates, cocaine, barbiturates, PCP, amphetamines, alcohol, and benzodiazepines on each specimen. The laboratory results will be available to [name] and the study assistant via the HIPAA compliant, encrypted, password protected clinical information system. They will not be reviewed until after the subject has completed the study to protect the masking.

We will conduct a blood test at screening and at weeks 4 and 8.  Laboratory markers of inflammation including IL1b, IL4, IL6, IL10, VCAM-1 and TNFα, tryptase, and substance P and safety laboratory tests of renal function, liver function, complete blood count and reticulocytes and pregnancy at screening and at weeks 4 and 8.

Assessments at weeks 2 and 6 are safety assessments only which consist of self reported adverse events, the PQ-B and the CSSR. These visits may be completed as in person or telemedicine visits.

## 8.2 Safety and Other Assessments

We have well-established protocols to screen for medical and psychiatric eligibility. [name] conduct a thorough medical and psychiatric screening of potential participants who meet initial screening criteria and who provide informed consent. Eligibility criteria are detailed in Human Subjects and the determination of eligibility will include:

- Second screening visit. At the screening visit with [name] potential participants will be further assessed for medical and psychiatric eligibility. A physical examination will be performed, women with reproductive potential will take a pregnancy test, and psychiatric disease and substance use disorders will be assessed using the following standardized instruments: 1) the Prodromal Questionaire -Brief (PD-B) a short structured interview to assess for psychotic symptoms; and 2) the Columbia Suicide Severity Rating Scale (CSSR).

Throughout the proposed study, [name] will be responsible for continual medical oversight of patients. All participants will be given oral and written instructions about management of adverse medication effects and emergency contact information prior to initiating medication therapy.

Adverse events, including cardiovascular events, will be assessed at weeks 2, 4, 6, and 8 by asking participants about symptoms that emerged or worsened since the start of medication treatment, whether or not they were thought to be related to study medication. Participants will be asked about treatment-emergent symptoms using both a structured interview and open-ended questions. In the structured interview, we will assess for the presence of specific symptoms reported among ≥ 5 % of participants receiving dronabinol in published research, including (but not limited to) nausea, headache, anxiety, dizziness, paranoid thoughts, sleepiness, euphoria. We chose the threshold of 5% as the majority of published dronabinol studies did not report symptoms that occurred in <5% of participants. Treatment emergent psychiatric symptoms will be further assessed using structured psychometric instruments at each research visit (as described below). All documented adverse events will be documented in case report forms and followed up to resolution or end of study.

In order to protect patients from the potential psychiatric risks of dronabinol we developed and implemented detailed protocols for the assessment of incident psychiatric symptoms. Psychiatric symptoms and suicidal ideation will be assessed at weeks 2, 4, and 8, using the PD-B I and the CSSR. If participants meet diagnostic criteria for any new DSM-V Axis I diagnoses, or report suicidal ideation, it will trigger immediate clinical intervention.

We will conduct a blood test at screening then safety laboratory tests to evaluate for possible changes in renal function, liver function, complete blood count and reticulocytes and pregnancy at weeks 4 and 8.

